#### The telerehabilitation service

Study nurse led training is given to patients within 7 days after randomization. They are provided with some background and general information regarding the study design, content and main hypotheses of Telerehab III. Patients are taught about how to install the Telerehabilitation program on their computer and how to use the accelerometer. This presentation is followed by a one hour lasting practical training session in which patients are familiarized with the accelerometer and associated webpage. They are instructed to install the program at home; however in case of questions or technical difficulties, they are provided with technical support.

#### The exercise training protocol

Intervention patients are prescribed with literature based [11–13], patient-specific exercise training protocols. These exercise protocols are based on maximal CPET and calculated body mass index (BMI) at the start of study period. Patients with a high aerobic capacity (defined as VO2 peak ≥ 80 % predicted) are stimulated to exercise at an intensity of ≥ 100 steps/min, for at least 3 times/week and minimal session duration of 30 min; in order to increase the likelihood for significant changes in exercise tolerance [14]. Patients with a low aerobic capacity (defined as VO2 peak < 80 % predicted) were allowed to choose themselves the intensity of exercise sessions. In addition, volume of exercise depended on body mass index: The instructed volume of steps was set at 10.000-12.000 steps/day for patients with a BMI > 30 kg/m2 and 8.000-10.000 steps/day for patients with a BMI < 30 kg/m2 (Fig. 2).

**Fig. 2 Fig2:**
[figure not shown]
Algorithm defining intensity, frequency, duration and volume characteristics of exercise training protocols used in the telerehabilitation program

Patients are instructed to wear the accelerometer during entire study period, except while bathing and/or sleeping. Due to the accelerometer’s storage capacity of 14 days, patients upload data at least every 2 weeks to a secure webpage with an USB-connection. The webpage displays uploaded physical activities thereby enabling patients to self-monitor these data. Based on the uploaded data a semi-automatic telecoaching system, provides patients with weekly feedback via e-mail and/or SMS. This feedback is intended to encourage patients to achieve the goals as predefined in the patient-specific exercise training protocols.

Uploaded accelerometry data are automatically transmitted in an encrypted manner to the telerehabilitation’s local server. All procedures are in compliance with confidentiality standards for medical data (De Wet op het Privéleven met Betrekking tot de Behandeling van Persoonlijke gegevens [W 1998-12-11/54]). Authorized medical staff treating the patient is granted unconstrained access to the patients’ data, whereas restricted access to anonymized data is granted to other local staff and researchers.

#### The dietary and smoking cessation telecoaching program

Intervention patients receive weekly dietary and smoking cessation advice, sent by email and/or SMS according to the patients’ preferences. The dietary telecoaching program includes a module for diabetes mellitus, for arterial hypertension, for obesity and a healthy module. Cardiovascular risk factor profiling at entry of study determines which module(s) are prescribed for each patient. Key to the diabetes mellitus module is the restriction of fast carbohydrates (monosaccharides), energy rich nutrition and ethanol containing beverages. The arterial hypertension and obesity modules focus on salt restriction (<5 g/day) and energy intake reduction respectively. Healthy diet includes recommendations based on the food triangle [15]. The smoking cessation telecoaching program includes information on major risks associated with smoking, the health benefits of smoking cessation and nicotine replacement therapy. It provides smokers with encouraging messages towards smoking cessation.

### Conventional cardiac rehabilitation care

Patients in the control group follow the conventional center-based CR program; including 45 pluridisciplinary rehabilitation sessions focusing on healthy diet, psychosocial wellbeing, behavioural change, risk factor modification and exercise training. The exercise training sessions are scheduled 2 to 3 times/week; with an average session duration of 45 min. Training intensity is progressively increased from the ventilatory anaerobic threshold to the respiratory compensation point. Main exercise modalities include walking/running and cycling.

These patients are instructed to wear the accelerometer three times; at study start, after 6 weeks and at the end of study period for observation purposes only. The sensors are taped at the hospital using black tape, making it impossible for the patient to see the registered physical activity data. Data uploading is performed by study nurses of the respective hospitals, patients cannot consult the webpage with uploaded data. They do not receive physical activity, smoking cessation or dietary telecoaching by email and/or SMS.

### Study endpoints

The primary endpoint is peak oxygen consumption (VO2 peak). The first secondary endpoint is daily physical activity, defined as the total number of daily low intensity and high intensity steps.

Other secondary endpoints include:Cardiovascular risk factor control (body weight, blood pressure, blood lipid profile, blood glucose level and HbA1c) at 6 weeks and 6 monthsHeartQol quality of life score at 6 weeks and 6 months, adjusted for baselineIPAQ physical activity score at 6 weeks and 6 months, adjusted for baselineEQ-5D score at 6 weeks and 6 months, adjusted for baselineDays lost due to cardiovascular rehospitalizationDays lost due to hospitalization for any reasonTime to first cardiovascular rehospitalizationTime to first hospitalization for any reason.

Outcome assessors were blinded to treatment allocation.

### Clinical Endpoint Committee

A Clinical Endpoint Committee (CEC), composed of three specialists in internal medicine (with at least two of them cardiologists), will classify all rehospitalizations. This classification will be based on the completion of templates defining the criteria and definitions for cardiovascular and/or non-cardiovascular rehospitalizations.

### Statistical analysis

The statistical analysis will be performed according to the Intention-to-treat principle. For continuous data, the Shapiro-Wilk test will investigate whether normal distribution is present. When data are not normally distributed, the Mann–Whitney U-test will be used for the comparison between groups; and the Wilcoxon Signed Rank test will be used for the comparison within groups. When data are normally distributed the One Way ANOVA repeated measures test will be used for both between and within group analysis. Kaplan-Meier plots and log-rank tests will be used to compare censored time-to-event data; for the time to first cardiovascular rehospitalization and time to first rehospitalization for any reason. The statistical software package SPSS will be used for analysis. P-values <0,05 will be considered statistically significant.

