### Sample size

The sample size calculation is based on a 20 % effect size of VO2 peak , which is comparable to the effect reported by Frederix et al. in their Telereab II study [9]. In order to attain a minimal power of 95 %, at an alpha error probability < 0,05; 140 patients should be recruited when taking into account a dropout rate of 30 % during follow-up.

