### Outcome assessments

At entry of study a complete medical history, clinical assessment (including measurement of body mass index, waist circumference, blood pressure and heart rate) and treatment scheme are collected. A transthoracic echocardiography (TTE) evaluating LV systolic function (using Simpson’s method and/or eye balling), LV diastolic function (E/A ratio, DT, IVRT and pulmonary venous flow curves) and presence/absence of increased left atrial filling pressures (average E/E’) is planned, when no recent TTE (performed < 6 months earlier) is available. Every patient performs a maximal cardiopulmonary exercise test (CPET) with breath-by-breath gas exchange analysis. The criteria for defining maximal CPET are an achieved heart rate > 85 % of the maximal predicted heart rate, an achieved Respiratory Exchange Ratio (RER) > 1,1, and/or achieving a plateau on the VO2 curve. During CPET, we will record RER, resting and maximal heart rate, resting and maximal systolic and diastolic blood pressure, resting and maximal rate pressure product, VO2 peak, maximal work load, ventilatory anaerobic threshold, respiratory compensation point and the oxygen uptake efficiency slope. We will use the recommendations provided by Wasserman et al. to predict VO2 peak and to calculate % of predicted VO2 peak [10]. Fasting blood samples are taken, to determine blood glucose, HbA1c, CRP level and lipid profile. Patients are asked to complete a quality of life questionnaire (HeartQol), a questionnaire to assess self-reported physical activities (IPAQ) and the EQ-5D questionnaire. After randomization, study visits were scheduled after 6 weeks as well as at the end of study period. During these visits, clinical assessment, treatment scheme collection and maximal CPET are performed. Patients are again asked to complete the HeartQol, IPAQ and EQ-5D questionnaires. Blood sampling is only repeated after study completion (Fig. 1).

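### The analysis is labelled intention-to-treat, but the repeated-measures ANOVA named for normally distributed outcomes leaves out every patient with a missing exercise test, and 30% dropout is planned for

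*Protocol article*

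**What the plan says.** All of this is in the protocol article.

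- **Principle** (Statistical analysis): "The statistical analysis will be performed according to the Intention-to-treat principle".
- **Method if normality is not rejected** (same section): "When data are normally distributed the One Way ANOVA repeated measures test will be used for both between and within group analysis".
- **Method otherwise** (same section): "When data are not normally distributed, the Mann–Whitney U-test will be used for the comparison between groups".
- **Software** (same section): "The statistical software package SPSS will be used for analysis".
- **Measurements** (Outcome assessments): every patient has a maximal CPET at entry. Then, "After randomization, study visits were scheduled after 6 weeks as well as at the end of study period", and "During these visits, clinical assessment, treatment scheme collection and maximal CPET are performed". The primary endpoint, VO2 peak, is therefore planned at three time points.
- **Expected loss** (Sample size): "140 patients should be recruited when taking into account a dropout rate of" 30% during follow-up.

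The article describes no imputation, mixed model or other means of keeping a patient whose CPET is missing.

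**The concern.** Intention-to-treat means that randomised patients are compared as allocated. Repeated-measures ANOVA (read here as visit within patients and arm between patients) needs a value at every visit, and the standard SPSS procedure deletes any patient who lacks one. The plan expects almost a third of patients to be lost. The named method would therefore set aside the very patients whom the stated principle is meant to keep, together with any 6-week result they had already given.

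Once patients are selected by whether they completed, randomisation no longer guarantees comparable groups. If the reasons for leaving differ by arm and relate to fitness, a completers comparison can create or hide a difference. Differential loss is plausible here. Intervention patients wear the accelerometer throughout, upload at least every two weeks and receive weekly messages, while controls wear it three times and receive no telecoaching.

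**Working it through.** **1. How many patients are affected.** Inputs: 140 patients and 30% dropout (Sample size).

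- 140 × 0.30 = 42 lost; 140 − 42 = 98 with complete follow-up.
- In reverse, 98 / (1 − 0.30) = 140, which matches the stated total. But 107 × 1.30 = 139.1 also rounds up to 140, so the article does not establish that 98 was the planned number analysed.
- Patients who leave before 6 weeks have no 6-week CPET to discard; those who leave later do. Isolated missed tests would add to the exclusions.

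**2. What each branch keeps at 30% loss by end of study.**

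| Branch | 6-week comparison | End-of-study comparison |
|---|---|---|
| Repeated-measures ANOVA | complete patients only, about 98 | about 98 |
| Mann–Whitney at a visit | all measured at 6 weeks | about 98 |

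Neither branch, as named, uses all 140 at the end of the study.

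**3. Illustration of the bias.** None of these inputs is in the article; all are assumptions.

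- 70 patients per arm, no true effect, SD 1 at each visit, correlation 0.7 between every pair of visits.
- Control dropout after 6 weeks: 30% at random.
- Intervention dropout after 6 weeks: probability 1 / (1 + exp(1.2 + 1.5z)), where z is the 6-week change divided by its SD, √0.6 = 0.775. Poor responders leave more often; overall loss is again about 30%.

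Results over 3,000 simulated trials:

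- mean number of completers: 98.1;
- spurious intervention gain in baseline-to-end change among completers: 0.13 SD;
- rejection rate of the group-by-time test in the complete-case ANOVA: 30% instead of 5% (a separate simulation of the same kind of dropout gave 33%);
- estimated difference when all patients' baseline and 6-week values are used: 0.007 SD.

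With 30% random loss in both arms, error rates were 5–6%, as they should be.

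**4. Where that bias sits.**

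- Variance of the 6-week change: 2 × (1 − 0.7) = 0.6. Its covariance with the baseline-to-end change: 0.7 − 0.7 − 0.7 + 1 = 0.3. Slope: 0.3 / 0.6 = 0.5.
- A 0.13 SD shift in change at the end thus goes with 0.13 / 0.5 = 0.26 SD in change at 6 weeks. The group-by-time test picks up both.
- For baseline the slope is (0.7 − 1) / 0.6 = −0.5, so retained intervention patients start about 0.13 SD lower. Their raw end-of-study mean is shifted by −0.13 + 0.13 = 0.
- A test of baseline-to-end change alone, with 49 per arm, has standard error 0.775 × √(2/49) = 0.156. The shift is 0.13 / 0.156 = 0.83 standard errors, which gives about 13% false positives.

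The 30% therefore belongs to the three-visit group-by-time test, and the 0.13 SD to change from baseline.

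**The case against.** The strongest reply is that the article is condensed. It is silent on missing data, and an analysis plan not shown could specify imputation before the ANOVA, which would remove the conflict. Silence alone would indeed be no finding. But the article does fix a method, and that method, as ordinarily run, excludes the dropouts it plans for while the result is called intention-to-treat. That conflict stands on the text. Naming SPSS proves nothing either way, since SPSS can also fit a mixed model.

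Three further objections stand and limit the point:

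- Loss of patients with any missing visit belongs to the ANOVA branch only. Mann–Whitney at 6 weeks keeps those who leave afterwards.
- The article gives no dropout by arm. Unequal or selective loss is plausible, not shown.
- The 30% is a planning allowance; actual loss may be smaller or larger.

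A reader might also infer a much larger bias. If the 30% of controls with the lowest 6-week VO2 peak leave and intervention loss is random, retained controls average 0.497 SD too high at 6 weeks. At correlation 0.7 that is 0.497 × 0.7 = 0.348 SD at the end of the study. The arithmetic is right for raw late means. The same 0.348 SD also appears at baseline, however, so the bias in baseline-to-end change is about zero. The scenario also makes control dropout the selective one, although the heavier burden falls on the intervention arm.

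Nor can that figure be set against a planned effect in SD units. The article gives no SD, and a detectable effect of about 0.73 SD arises only by assuming 98 analysed and a two-sided comparison of two means.

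**Conclusion.** The point holds. The stated principle and the named method do not fit together for normally distributed VO2 peak, and the non-normal branch does not restore an analysis of all randomised patients at the end of the study. Up to about 42 of 140 patients are affected if dropout reaches the planned 30%.

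The harm is mainly potential bias. Power was already allowed for through the sample size, although discarding observed 6-week tests also wastes information. The size of the bias depends wholly on who leaves: none with random loss, and about 0.13 SD in change with about 30% group-by-time false positives under the assumptions in step 3. Other patterns could bias the between-arm means instead, or act against the intervention. These figures show what can happen; they do not predict this trial's error.

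The documents do not support saying that the primary result is bound to be an analysis of 98 completers. The branch depends on a normality test, and an unseen plan could add imputation.

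**What to change.** Make the primary analysis of VO2 peak a likelihood-based mixed model for repeated measures (SPSS MIXED), with arm-by-visit, baseline VO2 peak and hospital. Include every randomised patient with any post-baseline VO2 peak, analysed as allocated. This keeps the 6-week test of those who leave later and is valid when dropout depends on observed values. Add one sensitivity analysis for data not missing at random, covering all randomised patients. Report the repeated-measures ANOVA on completers as secondary.

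The cost is a change of wording and a little more analysis work, with no additional patients. The price in assumptions is that the primary result relies on data being missing at random. Patients with no post-baseline CPET still contribute only through the sensitivity analysis, so their number should be reported by arm.

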The Telerehab III trial is a randomised, controlled, multi-center study designed to investigate the long-term effectiveness of the addition of a patient-tailored, internet-based telerehabilitation program implementing multiple CR core components and using both telemonitoring and telecoaching strategies to conventional CR; when compared to conventional center-based CR alone. The primary hypothesis is that the addition of telerehabilitation increases patient’s physical fitness and activity level with greater magnitude, when compared to usual care. Secondary endpoints include cardiovascular risk factor control, quality of life and (non-) cardiovascular rehospitalizations.

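### Within-group significance tests sit beside the between-group test under one 0.05 rule, and the protocol does not say that only the between-group test decides effectiveness

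*Protocol article*

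**What the plan says.** The Background section of the protocol article puts the trial's question as a comparison of arms: "The primary hypothesis is that the addition of telerehabilitation increases patient’s physical fitness and activity level with greater magnitude, when compared to usual care".

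The Statistical analysis section then plans two kinds of comparison for continuous data, with the branch chosen by a Shapiro-Wilk test:

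- Non-normal data: "the Mann–Whitney U-test will be used for the comparison between groups", and "the Wilcoxon Signed Rank test will be used for the comparison within groups".
- Normal data: "the One Way ANOVA repeated measures test will be used for both between and within group analysis".

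The section closes with one rule for all of these: "P-values <0,05 will be considered statistically significant". It does not call the within-group tests descriptive, and it does not say that the between-group test alone decides effectiveness.

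Under Study design and Conventional cardiac rehabilitation care, both arms attend centre-based rehabilitation. The control programme has exercise training 2 to 3 times a week.

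**The concern.** A within-group test compares patients with their own baseline and makes no use of the randomised comparison. Both arms train, so change within an arm is to be expected whether or not telerehabilitation adds anything. A significant change in one arm and a non-significant change in the other is not evidence that the arms differ. The two results can fall on opposite sides of 0.05 when the true changes are equal.

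The normal branch makes this sharper. A one-way repeated-measures ANOVA, as named, has a single factor, time. It has no arm term and no arm-by-time term, so read literally it yields only a time effect and cannot supply the between-group analysis assigned to it.

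At stake is how the results are read. A non-significant between-arm result could be reported next to a significant change in the intervention arm, with no statement in the plan of which one answers the question.

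**Working it through.** The protocol gives no error rate for this pattern, so there is no figure of its own to reproduce. The check asks how often the pattern would arise by chance if the arms truly changed by the same amount.

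**Inputs**

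- Patients per arm: 140 recruited, 30% dropout (Sample size) and equal allocation (Study design). 140 × 0.70 = 98, and 98 / 2 = 49.
- Threshold: 0.05 (Statistical analysis). Sidedness is not stated; two-sided is assumed.
- Standardised change d, meaning the mean change divided by the SD of change. The protocol gives no SD of change. A range is therefore assumed, with the same d in both arms.

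**Formula**

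Let p be the probability that a paired t-test in one arm shows significant improvement: the upper tail of a noncentral t distribution with 48 degrees of freedom and noncentrality d√49 = 7d, beyond the two-sided 0.05 critical value. The arms are independent and share the same d, so

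P(intervention significant, control not) = p(1 − p).

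**Results, 49 per arm**

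| Common change d (SD) | p | p(1 − p) |
|---|---|---|
| 0.1 | 0.101 | 0.101 × 0.899 = 0.091 |
| 0.2 | 0.278 | 0.278 × 0.722 = 0.201 |
| 0.28 | 0.484 | 0.484 × 0.516 = 0.250 |
| 0.3 | 0.539 | 0.539 × 0.461 = 0.248 |
| 0.4 | 0.783 | 0.783 × 0.217 = 0.170 |
| 0.5 | 0.929 | 0.929 × 0.071 = 0.066 |

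The product p(1 − p) cannot exceed 0.5 × 0.5 = 0.25. It reaches that value when within-arm power is 50%, which at 49 per arm is a change of about 0.28 SD. With all 70 per arm analysed, the values at d = 0.1, 0.2, 0.28, 0.3, 0.4 and 0.5 are 0.112, 0.235, 0.231, 0.211, 0.082 and 0.015.

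**Simulation check, 49 per arm, equal true change**

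- At 0.28 SD the pattern appeared in 24.8% of trials with paired t-tests and 23.9% with signed-rank tests.
- At 0.28 SD it appeared together with a non-significant between-arm test in 22.5% of trials (paired and two-sample t) and 21.5% (signed rank and Mann–Whitney).
- With no change in either arm the pattern appeared in 2.4% of trials, at 0.5 SD in 6.8%, and at 0.8 SD in about 0%.
- The two-sample t-test between arms was significant in 4.5% to 5.2% of trials across the scenarios run at 49 and 70 per arm, so its error rate stays at the nominal 5%.

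**The case against.** The strongest reply is that the plan does not make this error. Both branches name a between-group comparison, the hypothesis in Background is between-arm, and VO2 peak is the single primary endpoint. A general sentence on the threshold does not turn every test into a decision rule, and a within-arm P-value is a valid statement that the arm changed. A condensed article may also leave the ranking of tests to a fuller document.

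Most of this stands, and it rules out four stronger readings that a reader might infer:

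- *The sponsor will take a discordant pattern as an effect.* No section says so.
- *The within-arm tests have equal standing as tests of efficacy.* A shared threshold does not establish that.
- *The false-positive rate is inflated tenfold (25% against 2.5% in the favourable direction).* That sets the planned test against a decision rule found nowhere in the protocol; the planned between-arm test is not inflated.
- *A quarter of null trials would mislead.* The 25% is the ceiling for any two independent arms, and the rate is far lower when the shared change is large or absent.

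The scope is also limited. A separate within-group test is named outright only in the non-normal branch. Whether VO2 peak enters that branch depends on the normality test, and days lost to hospitalisation have no baseline to test against.

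The reply does not remove the point itself. The section goes beyond leaving detail out: it prescribes within-group testing, applies the significance rule to it, and in the normal branch names a procedure with no arm term. Those are stated choices that do not match the stated question.

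**Conclusion.** The point holds as a minor one. The protocol plans within-group significance tests next to the between-group test under one 0.05 rule and does not say that only the latter decides effectiveness. Those tests cannot show an added effect of telerehabilitation.

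If the discordant pattern were read as an effect, the chance of it under equal true change would be about 7% to 25% for common changes of 0.1 to 0.5 SD. This assumes 49 analysed per arm, two-sided tests, independent arms and approximately normal changes. The documents do not show where in the range the trial would fall, because they give no SD of change. The risk is one of misreading the results; the planned between-arm comparison keeps its 5% error rate.

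**What to change.** In the Statistical analysis section:

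1. Report within-arm change descriptively, as mean or median change with a 95% confidence interval and no P-value.
2. State that effectiveness for each endpoint rests only on the between-arm comparison, reported as a between-arm difference with a 95% confidence interval.
3. In the normal branch, name a test that contains an arm term or an arm-by-time term.

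This is a change of wording and needs no new data. The article describes the trial as ongoing, so the change could be made before analysis. The cost is that the sponsor gives up the within-arm P-values.

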## Methods/Design

### Study design

Telerehab III is a multi-center, prospective, randomized, controlled clinical trial recruiting one hundred and forty stable coronary artery disease (CAD) and/or chronic heart failure (CHF) patients (Fig. 1). Patients are randomized in equal proportions to one of two groups: internet-based telerehabilitation in addition to center-based rehabilitation (intervention group) or center-based rehabilitation alone (control group). Patients are enrolled after completion of the first six weeks of their phase II center-based rehabilitation program. They are followed for a minimum of 6 months and a maximum of 25 months.

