### Randomization

Patients are assigned to one of two treatment arms by a central computerized randomization system. Block randomization is used to ascertain equal distribution of patients in the intervention and control group in the different recruiting hospitals. In order to achieve a balance of relevant patient characteristics in both study arms, it will be assessed whether patients are matched for age, gender, cardiac disease category and cardiovascular risk factor profile. When intervention and control patients are not matched for these characteristics, a second randomization process will be done to ascertain matching. Investigators are unaware of the randomization sequence.

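### For normally distributed data the article names a one-way repeated-measures ANOVA, which has no treatment-arm factor, so the test that decides the VO2 peak comparison is misnamed or left undetermined

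*Protocol article*

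**What the plan says.** The Background section sets out a between-arm superiority hypothesis: "the addition of telerehabilitation increases patient’s physical fitness and activity level with greater magnitude, when compared to usual care". The Study design section gives the allocation: "Patients are randomized in equal proportions to one of two groups". The Study endpoints section makes VO2 peak primary, with no time point. VO2 peak is measured at entry and at two later visits (Outcome assessments: "After randomization, study visits were scheduled after 6 weeks as well as at the end of study period").

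For continuous data the Statistical analysis section has two branches, chosen by a Shapiro–Wilk test. In the non-normal branch, "the Mann–Whitney U-test will be used for the comparison between groups", with the Wilcoxon signed-rank test used within groups. In the normal branch one test does both jobs: "When data are normally distributed the One Way ANOVA repeated measures test will be used for both between and within group analysis".

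The Study endpoints section lists HeartQol "quality of life score at 6 weeks and 6 months, adjusted for" baseline, and says the same of IPAQ and EQ-5D. It does not say this of VO2 peak. The Randomization section states: "Block randomization is used to ascertain equal distribution of patients in the intervention and control group in the different recruiting hospitals".

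**The concern.** The only factor in a one-way repeated-measures ANOVA is the repeated one, here visit. Its F-test asks whether mean VO2 peak changes over visits and contains no term for treatment arm. Both arms take part in centre-based exercise training during the trial, so some change over time is plausible in both, whether or not telerehabilitation adds anything. A p-value for time would answer a different question from the one in the Background section.

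If the label is loose and a mixed ANOVA with arm and time was intended, a second question opens. That model reports a group main effect, a time effect and an arm-by-time interaction. The article does not say which is the test of the primary hypothesis. The group main effect averages the pre-treatment visit into the contrast and so dilutes any effect. An analyst could follow the sentence faithfully and report any of the three.

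**Working it through.** **Inputs from the article.** Two arms, 1:1. 140 patients less 30% dropout gives 140 × 0.70 = 98, or 49 per arm. VO2 peak is measured at three visits.

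**Assumptions, because the article gives no SD or correlation.** SD of 1 at each visit; equal correlation ρ between visits (0.7, with 0.5 as the alternative); true arm effect 0.5 SD; two-sided 5% level. No figure of the plan can be reproduced here: the Sample size section does not state the test, SD or correlation behind its 140.

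**1. The test as named (time only).** The noncentrality is λ = N·Σ(m_t − m̄)²/(1 − ρ), with 2 and 194 df. Suppose there is no arm effect and both arms improve to 0.3 SD.
- Immediate gain, means (0, 0.3, 0.3): Σ = 0.06, so λ = 98 × 0.06/0.3 = 19.6 and p < 0.05 in 98% of trials.
- Gradual gain, means (0, 0.15, 0.3): Σ = 0.045, so λ = 14.7 and p < 0.05 in 94%.
- At ρ = 0.5 the rates are 87% and about 75%.

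Conversely, with a true 0.5 SD arm difference (+0.25 against −0.25) and no average time change, simulation shows the test rejecting in only 3–5% of trials for ρ from 0.5 to 0.85. It tracks time, not treatment.

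**2. Mixed ANOVA, group main effect.** The ratio is δ̄ / √[(2/49)(1 + 2ρ)/3], where δ̄ is the arm difference averaged over the three visits. At ρ = 0.7 the denominator is √(0.0408 × 0.8) = 0.181.
- Effect at both follow-up visits: δ̄ = (0 + 0.5 + 0.5)/3 = 0.333, ratio 1.84, power 45%.
- Effect at the late visit only: δ̄ = 0.167, ratio 0.92, power 15%.

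**3. Mixed ANOVA, arm-by-time interaction.** λ = (49/2)·Σ(δ_t − δ̄)²/(1 − ρ), with 2 and 192 df.
- Effect at both follow-ups, or late only: Σ = 0.1667 in either case, so λ = 24.5 × 0.1667/0.3 = 13.6 and power is 92%. At ρ = 0.5, λ = 8.2 and power is 72%.
- Effect building gradually (0, 0.25, 0.5): Σ = 0.125, λ = 10.2, power 82%. At ρ = 0.5, 59%.

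**4. ANCOVA on the late value.** The ratio is 0.5/√[(2/49)(1 − ρ²)]. At ρ = 0.7 this is 0.5/0.144 = 3.47, power 93%. At ρ = 0.5 it is 0.5/0.175 = 2.86, power 81%.

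**5. Unadjusted comparison of late values.** 0.5/√(2/49) = 0.5/0.202 = 2.48, power 69% at any ρ.

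| Test of the arm effect | ρ = 0.7 | ρ = 0.5 |
|---|---|---|
| Group main effect, effect at both follow-ups | 45% | 52% |
| Group main effect, late only | 15% | 17% |
| Interaction, both follow-ups or late only | 92% | 72% |
| Interaction, gradual effect | 82% | 59% |
| ANCOVA, late value | 93% | 81% |
| Unadjusted late value | 69% | 69% |

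Simulation with 4,000 trials per scenario agrees to within one or two percentage points. With no arm effect and both arms improving, the interaction, the ANCOVA and the unadjusted comparison each reject in about 5–6% of trials.

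**6. Baseline adjustment, side by side.** Study endpoints promises adjusted HeartQol, IPAQ and EQ-5D scores. The between- and within-group methods named for continuous data are Mann–Whitney, Wilcoxon signed-rank and one-way repeated-measures ANOVA. None takes a baseline covariate.

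**The case against.** The best defence is that the sentence itself assigns the test to a between-group comparison. A time-only ANOVA has no between-group part, so the natural reading is a repeated-measures procedure with arm as the one between-patient factor. The stated hypothesis of a greater increase than usual care is then the arm-by-time interaction, which is valid and, at correlation 0.7, loses almost nothing against ANCOVA (92% against 93%). This largely stands. It makes misnaming the likeliest explanation. It does not tell the reader which F-test is primary, and the interaction does lose power when the effect builds gradually or the correlation is lower.

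A reader might infer that the trial cannot test its hypothesis, or that it will produce false positives in more than nine of ten trials. The document does not support either. Nothing in it says that a pooled time effect would be taken as evidence for telerehabilitation, and the Mann–Whitney branch compares the arms directly.

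A reader might also infer that leaving VO2 peak unadjusted for baseline invalidates the test. It does not: the unadjusted randomised comparison holds its 5% error rate and only loses power. No adjustment is promised for that endpoint.

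Finally, the adjusting model and the handling of hospital are commonly left to an analysis plan. For hospital that is a fair answer, and the point is optional. For the questionnaire scores it is only partly so, because the article does name its methods for continuous data and they do not match its own endpoint definitions.

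**Conclusion.** The concern holds in limited form. In the normal-data branch, the test named for the between-arm comparison has no arm factor. On the more generous reading, the deciding contrast is unspecified among F-tests whose power for the same effect runs from about 15% to 92% (0.5 SD effect, correlation 0.7, 98 patients, equal correlations between visits). The interaction would be an acceptable test; the group main effect would be a poor one. Lack of baseline adjustment for VO2 peak is a matter of efficiency: 69% unadjusted against 93% adjusted at correlation 0.7, and against 81% at 0.5. The promised adjustment of the three questionnaire scores has no matching method and must be reconciled. The percentages depend on the assumed effect, correlation and pattern over visits. The absence of an arm term from the named test does not.

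**What to change.** Replace the sentence on normally distributed data with one arm-comparing model for VO2 peak, and state the time point at which it applies. Either of these would serve:
- ANCOVA of VO2 peak at that time point, with arm and baseline VO2 peak as terms.
- A mixed model over the 6-week and late visits with arm, time, arm-by-time and baseline VO2 peak, the primary result being the arm contrast at the late visit.

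Report the adjusted difference between arms with its 95% confidence interval. Use the same model for HeartQol, IPAQ and EQ-5D, which gives the promised baseline adjustment a method. Label within-group tests as descriptive and not as evidence of a treatment effect. Hospital may be added as a term because randomisation is blocked within hospital; this is optional.

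The cost is a change of analysis wording. The trial is described as ongoing, the visits and measurements are already scheduled, SPSS fits both models, and no extra data are needed.
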